#### Fatigue Scale-14

The aim of Fatigue Scale-14 is to investigate the subjective feelings in fatigue of the patients. The patients will choose “yes” or “no” based on the situation that suits them the most. The Fatigue Scale-14 consists of 14 questions, in which questions 1–8 are physical fatigue while questions 9–14 are mental fatigue. Among the 14 questions, 11 questions are positive scoring, which “yes” is scored as 1 mark, “no” is scored as 0 mark; 3 questions, which are questions 10, 13, and 14 are negative scoring, which “no” is scored 1 mark and “yes” is scored as 0 mark. The physical fatigue is calculated based on questions 1–8 and its maximum score is 8; the mental fatigue is calculated based on questions 9–14 and its maximum score is 6. The Fatigue Scale-14 is the sum of the physical fatigue and the mental fatigue, the maximum score is 14. The greater the value of the Fatigue Scale-14, the greater the fatigue degree [34].

#### Patient Health Questionnaire-9 Scale (PHQ-9)

The Patient Health Questionnaire-9 Scale is used to measure the patients’ depression and seriousness in medical populations clinically; the Patient Health Questionnaire-9 Scale has been carried out with the usage of medical populations in various setting. The Patient Health Questionnaire-9 Scale is used to assess the frequency of the 9 negative objects that occurred to the patients in the past fortnight. It is scored as 0 point if it is not at all; it is scored as 1 point if they occurred once every few days; it is scored as 2 points if they occurred once more than half a day; it is scored as 3 points if they occurred every day. The Patient Health Questionnaire-9 Scale is classified into categories in increasing seriousness which include 0–4, 5–9, 10–14, 15–19, and ≥ 20. A repeated longitudinal analysis will be used to evaluate the outcome of the Patient Health Questionnaire-9 Scale [35].

#### Pittsburgh Sleep Quality Index (PSQI)

The Pittsburgh Sleep Quality Index (PSQI) assesses sleep quality and disturbances over the duration of experiment [36, 37]. Nineteen individual items generate seven “component” scores: subjective sleep quality, sleep latency, sleep duration, habitual sleep efficiency, sleep disturbances, use of sleeping medication, and daytime dysfunction. The total score of these seven components is the global score.

#### Respiratory Symptoms (RS) Scale

Respiratory symptoms include cough, expectoration, fatigue, chest tightness, dyspnea, sore throat, nasal congestion, runny nose, and some other nonspecific symptoms [38, 39]. The severity of these symptoms will be recorded accordingly as 0–10, with 0 being no respiratory symptom and 10 being the most severe. A repeated longitudinal analysis will be used to evaluate these self-evaluation scales.

### Sample size calculation

The PASS software (PASS 11, NCSS, LLC, Kaysville, UT, USA) will be used to estimate the sample size utilizing two independent sample means (*α* = 0.05, *β* = 0.10). We will use the mMRC Scale as the primary efficacy outcome. Based on previous clinical studies on the effect of respiratory symptoms after KQG interventions, the mMRC Scale score in the control group is 0.74 with a standard deviation of 0.55, and the average mMRC Scale score in the treatment group is 1.52 with a standard deviation of 0.54 [25, 40, 41]. The target sample size will be 60 participants in each group based on 80% power, 5% type I error, and two-sided test, anticipating on maximum loss to follow-up of 20%.

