## Methods/design

### Study design

This will be a single-center, parallel-arm, superiority randomized controlled trial. A total of 60 patients will be recruited from the Shanghai Municipal Hospital of Traditional Chinese Medicine, Shanghai University of Traditional Chinese Medicine. All patients will be provided written informed consent at the time of recruitment. Patients with symptoms of dyspnea will be recruited and will have equal opportunity to be randomly assigned to either the BT group or KQG group. Only outcome assessors and statisticians will be blinded due to the limitations of the intervention methodology. Outcomes will be assessed and analyzed by the assessors at three time points (pre-intervention, 3 months post-intervention, and 3 months follow-up). Data management and statistics will be conducted at the School of Acupuncture-Moxibustion and Tuina, Shanghai University of Traditional Chinese Medicine (SUTCM). The flowchart in Fig. 1 illustrates the study design, and Fig. 2 shows the study schedule. Additional file 1 shows the Standard Protocol Items: Recommendations for Interventional Trials (SPIRIT) checklist.

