**Fig. 1 Fig1:**
[figure not shown]
Flow chart of the trial. The present study is a randomized controlled trial. Sixty patients will be included and randomized equally to two groups, a BT group and a KQG group. For 30 patients in each group, this trial will include a 12-week treatment period. During the treatment, patients in the BT group will receive breathing techniques intervention, while the KQG group will receive KQG intervention. Both the outcome assessments will be performed at 3 time points, namely the baseline, the end of the treatments at 12 weeks, and 12 weeks of follow-up subsequently

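### The sample-size section sets 60 per group and claims both 90% and 80% power, the rest of the protocol sets 60 in total, and the stated inputs lead to neither size

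*Protocol article*

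**What the plan says.** Only the protocol article is at hand. Its statements on size and power are these.

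- **Sample size calculation, opening sentence:** the method is "two independent sample means (*α* = 0.05, *β* = 0.10", so power is 90%.
- **Same section, inputs:** "the mMRC Scale score in the control group is 0.74 with a standard deviation of 0.55". For the KQG arm the assumed mean is 1.52 (SD 0.54). Loss to follow-up is put at no more than 20%.
- **Same section, conclusion:** "The target sample size will be 60 participants in each group based on 80% power, 5% type I error, and two-sided test". Power is now 80%, and 60 per group makes 120.
- **Study design:** "A total of 60 patients will be recruited from the Shanghai Municipal Hospital of Traditional Chinese Medicine".
- **Fig. 1 legend:** "For 30 patients in each group, this trial will include a 12-week treatment period".
- **Abstract and Interventions:** both also give 60 patients in total, and the abstract adds 1:1 allocation.

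Two other sections bear on what the inputs mean. Under Primary outcome measurements, mMRC grades run from 0 to 4 and a higher grade is worse dyspnea. Under Analysis of primary outcome, the primary endpoint is the mean change in mMRC from baseline.

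**The concern.** The only section that derives a sample size disagrees with the four places that merely state one, by a factor of two. It also gives two values of power. A complete set of inputs is printed, so the result can be checked, and it does not come out at either size.

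Two things are at stake. One is the enrolment target: a trial that stops at 60 has half the number its own justification calls for, and a trial that goes on to 120 has twice the number its design section allows. The other is the power claim: 80% is presented as a property of the design, and a reader would use it to judge what the trial was built to detect.

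**Working it through.** **Inputs, all from Sample size calculation.** Means 0.74 and 1.52; SDs 0.55 and 0.54; two-sided α = 0.05; power 80% or 90%; loss 20%. Allocation is 1:1 (abstract).

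**Step 1: effect size.**
- Difference: 1.52 − 0.74 = 0.78.
- Pooled SD: √[(0.55² + 0.54²)/2] = √[(0.3025 + 0.2916)/2] = 0.545.
- Standardised difference: 0.78/0.545 = 1.43.

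**Step 2: try to reproduce the stated size.** With the normal approximation, n per group = (SD₁² + SD₂²)(z₀.₉₇₅ + z_power)²/Δ².
- 80% power: 0.5941 × (1.960 + 0.842)²/0.6084 = 7.7, so 8.
- 90% power: 0.5941 × (1.960 + 1.282)²/0.6084 = 10.3, so 11.

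The noncentral t calculation, which fits the planned unpaired t-test, gives slightly more:

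| Power sought | Evaluable per group (t) | Power reached | Per group after 20% loss, n/0.8 | Total |
|---|---|---|---|---|
| 80% | 9 | 0.813 | 11.25, so 12 | 24 |
| 90% | 12 | 0.918 | 15 | 30 |
| 99% | 19 | at least 0.99 | 23.75, so 24 | 48 |

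Neither 30 nor 60 per group appears. A one-sided test needs fewer: 9 per group after loss at 80% power and 13 at 90%. Inflating by 1.2 in place of dividing by 0.8 changes a figure by at most one.

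**Step 3: power at the stated sizes, same inputs.**
- 30 per group less 20% = 24 evaluable: noncentrality 1.431 × √(24/2) = 4.96 on 46 degrees of freedom, power 99.8%.
- 60 per group less 20% = 48 evaluable: power above 99.99%.

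**Step 4: what would make the stated sizes right.** Keep the difference at 0.78 and solve for the SD.
- 24 evaluable per group: SD about 0.94 for 80% power, or 0.82 for 90%.
- 48 evaluable per group: SD about 1.35 for 80%, or 1.17 for 90%.

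The protocol gives 0.54 and 0.55.

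**Step 5: what 24 evaluable per group would detect, if SD 0.545 applied to the endpoint.** The detectable standardised difference is 0.826 at 80% power and 0.956 at 90%.
- 80%: 0.826 × 0.545 = 0.45 grade.
- 90%: 0.956 × 0.545 = 0.52 grade.

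**Step 6: what the inputs are.** The section calls them scores, but the endpoint is a change. Read as scores on a scale where higher is worse, 1.52 in the treatment group against 0.74 in the control group favours control. They make sense for a superiority hypothesis only if they are reductions from baseline or if the arms are transposed. The protocol does not say which. The SD in Step 5 is therefore conditional.

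**The case against.** Four points can be made for the protocol.

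1. **The size conflict may be a slip.** Four places agree on 60 in total and one spells out 30 per group; a stray phrase in one sentence is the likelier explanation. This is fair, and 60 in total is probably the plan. But the outlier is the section that justifies the number, and the slip would not explain the two powers or the failure to reproduce.

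2. **Enrolling more than the minimum is not an error.** This stands. Both sizes exceed what the inputs require. What fails is the claim that the size was derived from those inputs at that power.

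3. **A journal article condenses the full protocol.** That would excuse an omission. Here the inputs and the result are all printed, and they disagree.

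4. **A reader might infer more than the documents support.** One inference is that the trial is under-powered; on the stated inputs it is not. Another is that the target difference is missing, so that a null result would be uninterpretable. The means imply a target of 0.78, for which 24 evaluable per group give 99.8% power, and a confidence interval would inform in any case. What remains is narrower: the meaning and direction of the inputs are unresolved, so the 99.8% is only as sound as they are.

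**Conclusion.** The concern holds as a contradiction and a failed derivation. The stated sizes differ by a factor of two (120 against 60 in total), and the stated powers are 90% and 80%. The printed inputs call for 12 or 15 per group after 20% loss, so 30 per group is 2 to 2.5 times the calculated need and 60 per group is 4 to 5 times. Neither 80% nor 90% describes the power of either size for a difference of 0.78.

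This rests on an unpaired t-test with equal groups, on the printed means and SDs, and on dividing by 0.8 for loss. The 0.45 and 0.52 grade figures rest further on an SD of about 0.545 applying to the change from baseline, which the protocol does not establish. The true power stays unknown until the inputs are clarified.

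**What to change.** 1. State one total size throughout. If 60 in total is the plan, replace *in each group* in Sample size calculation with *in total, 30 per group*.
2. State one power and delete the other figure.
3. Say whether 0.74 and 1.52 are scores or changes from baseline, which arm each belongs to, and whether the SDs are those of the change.
4. Redo the calculation on the clarified inputs. Report the power, or the detectable difference, that the chosen size gives after 20% loss.

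If an SD of about 0.545 is confirmed for the change, the statement for 60 in total would be that 24 evaluable per group detect about 0.45 grade at 80% power, or about 0.52 if 90% is the power chosen. This should replace the justification built on 0.78. If both stayed, the section would imply two target differences. The sponsor would also need to say whether a difference of that size matters clinically, since the protocol offers no support for it.

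The cost is returning to the source of the inputs, one recalculation and a protocol correction. No extra patients are needed. The downside is a less tidy justification: a size fixed in advance, with the difference it can detect.

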### Randomization

After the baseline measures, we will use a random number generator (IBM, Chicago, IL, USA) to randomly assign eligible participants to either BT group or KQG group and the randomization sequence will be sealed into the sequenced opaque envelope. The participants who pass the screening will then receive the envelope. The Science and Technology Department, Acupuncture & Tuina Institute SHUTCM will be responsible for the randomization.

### Blinding

We will use a concealed randomization where neither participant nor researcher was aware of the randomization until after the baseline interview. None of the participants or clinicians will be blinded to treatment allocation after randomization, due to the specific exercise intervention. However, they will be blinded to the outcome assessment. Evaluation of the outcomes will be accomplished by independent evaluators (IEs), including the outcome assessors, the data managers, and the statisticians. IEs will be blinded until the clinical database is locked.

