**Methods/design:**

This is a parallel-design, two-arm, analyst assessor-blinded, randomized controlled trial. In total, 60 discharged patients with COVID-19 sequelae, aged from 20 to 80 years will be recruited and randomly assigned to the World Health Organization instructed breathing techniques (BT) group and the Kangyi Qiangshen Gong exercise prescription (KQG) group at a ratio of 1:1. The patients in the BT group will perform breathing techniques exercise, and the patients in the KQG group will perform KQG exercise. Both groups will perform exercises twice a day for 3 months. The primary outcome will be measured with the Modified Medical Research Council Dyspnea Scale, and the secondary outcomes will include the Modified Borg Scale, Fatigue Scale-14, Patient Health Questionnaire-9 Scale, Pittsburgh Sleep Quality Index, and the Respiratory Symptoms Scale. Clinical scales will be assessed at three points (pre-exercise, 3 months post-exercise, and 3 months follow-up). Adverse events will be recorded for safety assessment.

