### Data collecting and monitoring

Data monitoring will be conducted by the Science and Technology Department of Acupuncture &Tuina Institute, SHUTCM. Clinical test data will be captured through case report forms (CRFs) by paper questionnaires or by online data capture applications and store in a secured location. Confidentiality will be maintained through the assignment of an encrypted number code. Data entry was double-checked for accuracy. The test data will be locked and analyzed by two statisticians under the supervision of a third statistician and the administrators. Then, the test data will be recorded on the sub-website of China Clinical Trial Center (http://www.medresman.org.cn/login.aspx) electronic data management system. The electronic database will be closed after data entry is completed. The administrators are required to report weekly data monitoring progress to the Steering Committee regularly, including the accuracy and reliability of data.

Trial auditing involves periodic independent review of core trial processes and documents, such as data monitoring and scheduling monitoring. Data monitoring will be conducted by the Science and Technology Department of Acupuncture &Tuina Institute, SHUTCM. The monitors will verify that all adverse events were documented in the correct format and are consistent with protocol definition. The monitor will verify the following variables for all patients: initials, date of birth, sex, signed informed consent, eligibility criteria, date of randomization, treatment assignment, adverse events, and endpoints. Scheduling monitoring visits will be a function of COVID-19 patient enrollment, site status, and other commitments. The investigators must be available to meet with the monitors. If a problem is identified during the visit (i.e., inadequate or insufficient staff to conduct the study, missing study documents), the monitor will assist the site in resolving the issues. The focus of the visit/electronic monitoring will be on source document review and confirmation of adverse events.

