#### Analysis of primary outcome

The primary outcomes will be evaluated at baseline, 12 weeks after the intervention, and follow-up. We will conduct sensitivity analyses for missing data (intention-to-treat analysis) and for adjustment of covariates of physical activity (adjusted intention-to-treat analysis). The primary endpoint is the mean change in mMRC Scales from baseline to the follow-up day. Baseline covariates included are sex, age category, history of cardiopulmonary disease, and body weight category. The whole outcomes scale will be measured at baseline. When normally distributed, the data will be analyzed with unpaired *t*-test for comparison between two groups, while for multiple comparisons one-way ANOVA and repeated measures (RM) ANOVA will be used. A sensitivity analysis using multiple imputation techniques (imputation using chained equations) will be included to assess the effect of missing data on the primary outcome. Besides, we will compare participants randomly allocated to BT group or KQG group, who received an allocated treatment that was deemed to be of high fidelity. The percentage of missing data is 20% and 5 imputed datasets will be used for analysis, which is the minimum recommended number. Prior to any analysis, any missing data pattern will be investigated and the reasons for missing data will be obtained and patterns will be investigated to judge the plausibility of missingness assumptions.

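### The trial is labelled analyst-blinded, but the statisticians' blinding is promised only until database lock, so the analysis itself is not stated to be blinded

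*Protocol article*

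**What the plan says.** The abstract (Methods/design) describes a "parallel-design, two-arm, analyst assessor-blinded, randomized controlled trial". The Study design section repeats the claim: "Only outcome assessors and statisticians will be blinded due to the limitations of the intervention methodology". Neither place says how long the blind lasts.

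The Blinding section does. It assigns outcome evaluation to "independent evaluators (IEs), including the outcome assessors, the data managers, and the statisticians" and then gives one end point for all three roles: "IEs will be blinded until the clinical database is locked".

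Data collecting and monitoring sets the order of events: "The test data will be locked and analyzed by two statisticians under the supervision of a third statistician and the administrators". It then describes recording in an electronic data management system and adds: "The electronic database will be closed after data entry is completed".

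Analysis of primary outcome names an unpaired t-test for normally distributed data and fixes multiple imputation by chained equations with 5 datasets as a sensitivity analysis. It requires missing-data patterns to be examined before any analysis, and it adds a comparison of participants "who received an allocated treatment that was deemed to be of high fidelity". Normality is to be judged by a Lilliefors-corrected Kolmogorov–Smirnov test (General analysis principles).

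**The concern.** Blinding an analyst has value while the analyst is analysing. Blinding to lock is enough for assessors and data managers, whose work is essentially finished by then. Statisticians start their main work after lock, so a promise that ends there does not cover the task that the label describes.

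This carries some weight here because few other safeguards remain. The Blinding section says that participants and clinicians will know the allocation, and the limitations section concedes that this may affect outcomes. The scales rest largely on what patients report. If judgements made on the locked data could be made with the arms known, they could lean, without intent, towards the hypothesis that KQG is better. Readers of the eventual report would also take analyst-blinded to mean something that the protocol does not secure.

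**Working it through.** The plan gives no figure to reproduce on this point, so the check sets the sections side by side.

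**1. Who is blinded, and for how long**

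| Section | What it establishes |
|---|---|
| Abstract, Methods/design | The analyst is blinded; no end point |
| Study design | Assessors and statisticians are blinded; no end point |
| Blinding | Statisticians are IEs; IEs are blinded up to database lock |
| Data collecting and monitoring | Data are locked, then analysed |

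Statisticians belong to the IEs, the IEs' blind is promised to lock, and analysis follows lock. So no stated blinding covers the analysis. The document also nowhere mentions coded arms or withholding the allocation after lock.

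**2. What is left to judgement at the analysis stage**

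- *Test choice.* The normality rule is stated in advance, but a test is named only for the normal case. The mMRC is an integer grade from 0 to 4, so the other case is likely. This was illustrated by simulation with assumed inputs: latent mean 1.5 to 2, SD 0.55 to 1.1, within-patient correlation 0.5, rounded to grades 0 to 4. Sizes were 30 per arm, 30 × 0.8 = 24 and 60 × 0.8 = 48, using the protocol's 20% loss. Lilliefors rejected normality of the change score in at least one arm in 99 to 100% of trials, and in both arms in 82 to 100%.
- *Missing data.* The imputation method and the number of datasets are fixed. Only the plausibility of the missingness assumption is judged from the data. That review precedes analysis and serves a sensitivity analysis.
- *Fidelity.* No threshold and no judge are named. The comparison is additional to the main one.

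**3. Can the effect be put as an error rate?**

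Not from these documents. The t statistic is (mean of A − mean of B) / SE. Exchanging A and B changes its sign but not its size, so the two-sided p-value is the same. The same holds for a two-sided rank test. An error rate computed by taking the smallest of several two-sided p-values therefore measures freedom to choose a test, and coding the arms would leave it unchanged. What coding removes is knowledge of which arm a choice favours.

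**The case against.** The strongest reply is that the blinding rule sets a minimum. It does not describe an unblinding step, and nothing says that statisticians receive the allocation at lock. The monitoring section is also unclear about which event is the lock: recording in the electronic system and closing of that database are described after the analysis. If that closure is what the Blinding section means, the blind would extend over the analysis. This stands. It rules out saying that the statisticians are unblinded at lock, but it does not supply a promise that they stay blinded, and the ambiguity is itself a reason to clarify.

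Second, blinding to lock has real value. It covers the assessors and data managers, and any analysis decision taken before lock. This also stands: a reader might infer that the blind protects nothing, and that would be wrong.

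Third, much of the analysis is pre-stated: the normality test, the imputation method and the 5 datasets. A reader might infer that imputation is left to the data, and the text does not support that. The analysis plan that the article mentions is not shown and may name the non-normal test and the fidelity threshold. Their absence is therefore no fault in itself. It shows only that, on this document, some judgements could fall after lock.

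Fourth, coding is not wholly free. The randomising department also monitors data, including treatment assignment and endpoints, and judging fidelity may require knowing which exercise was allocated. Both points stand and are dealt with in the fix. None of the four makes the blinding rule match the label.

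**Conclusion.** The concern holds in limited form. The label claims a blinded analyst, and the rule behind it guarantees the blind only to a point that, on the natural reading of the monitoring section, comes before analysis. This is a gap between a headline claim and the rule meant to deliver it, which a separate analysis plan would not close merely by fixing the methods.

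Its weight is modest. Of the three open judgements, one concerns a sensitivity analysis and one a supplementary comparison. Only the test for non-normal mMRC change touches the primary result. A reader might infer a measurable inflation of type I error from unblinding. The documents give no basis for one, for the reason in step 3 of the working.

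The conclusion assumes that lock in the Blinding section is the same event as the locking named immediately before analysis in the monitoring section. If it is a later event, the label may be accurate and the text needs only to say so.

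**What to change.** Amend the Blinding section so that the statisticians work on arms coded A and B, and the randomising department withholds the code until the primary analysis has been run and signed off. State which event counts as database lock.

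Settle the high-fidelity list from the adherence records before the code is broken. Any step that requires knowing the allocated exercise should be done by someone other than the statisticians. Since the randomising department also monitors the data, say that its staff do not pass the allocation to the statisticians.

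If this is not adopted, remove analyst from the blinding label in the abstract, and qualify the Study design sentence to say that the statisticians are blinded only up to lock.

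The change needs no further patients or data. Its cost is a few words of protocol text and minor handling of the code.
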